# Comparing the effectiveness of an enhanced MOtiVational intErviewing InTervention (MOVE IT) with usual care for reducing cardiovascular risk in high risk subjects: study protocol for a randomised controlled trial

**DOI:** 10.1186/s13063-015-0593-5

**Published:** 2015-03-25

**Keywords:** Cardiovascular disease, Physical activity, Diet, Accelerometer, Motivational interviewing, CBT, Primary care, Health trainers

## Abstract

**Background:**

Interventions targeting multiple risk factors for cardiovascular disease (CVD), including poor diet and physical inactivity, are more effective than interventions targeting a single risk factor. A motivational interviewing (MI) intervention can provide modest dietary improvements and physical activity increases, while adding cognitive behaviour therapy (CBT) skills may enhance the effects of MI. We designed a randomised controlled trial (RCT) to examine whether specific behaviour change techniques integrating MI and CBT result in favourable changes in weight and physical activity in those at high risk of CVD. A group and individual intervention will be compared to usual care. A group intervention offers potential benefits from social support and may be more cost effective.

**Methods/Design:**

Individuals aged between 40 and 74 years in 11 South London Clinical Commissioning Groups who are at high risk of developing CVD (≥20%) in the next 10 years will be recruited. A sample of 1,704 participants will be randomised to receive the enhanced MI intervention, delivered by trained healthy lifestyle facilitators (HLFs), in group or individual formats, in 10 sessions (plus an introductory session) over one year, or usual care. Randomisation will be conducted by King’s College London Clinical Trials Unit and researchers collecting outcome data will be blinded to treatment allocation. At 12-month and 24-month follow-up assessments, primary outcomes will be change in weight and physical activity (average steps per day). Secondary outcomes include changes in low-density lipoprotein cholesterol and CVD risk score. Incidence of CVD events since baseline will be recorded. A process evaluation will be conducted to evaluate factors which impact on delivery, adherence and outcome. An economic evaluation will estimate relative cost-effectiveness of each type of intervention delivery.

**Discussion:**

This RCT assesses the effectiveness of a healthy lifestyle intervention for people at high risk of CVD. Benefits of the study include the ethnic and socioeconomic diversity of the study population and that, via social support within the group setting and long-term follow-up period, the intervention offers the potential to support maintenance of a healthy lifestyle.

**Trial registration:**

This trial is registered with the ISRCTN registry (identifier: ISRCTN84864870, registered 15 May 2012).

## Background

### Epidemiology of cardiovascular disease and its risk factors

Cardiovascular disease (CVD) is the most common cause of death (and premature death), morbidity and disability in middle-aged and older people both in the United Kingdom and in other developed countries [1]. However, CVD is highly preventable as many of the major determinants of CVD are modifiable, including cigarette smoking, a diet high in saturated fat, high serum cholesterol, obesity, sedentary lifestyle, hypertension and diabetes [1-5]. The risk of CVD varies markedly between ethnic groups, with a higher rate of ischaemic heart disease in South Asians and a higher rate of cerebrovascular disease in Africans amongst those living in England and Wales [6].

Although CVD remains the most common cause of death in developed nations, mortality rates have been falling. Between 1981 and 2000, CVD mortality in the United Kingdom fell by 62% in men and by 45% in women [7]. Cohort studies [8] and prediction models [7] suggested that a fall in the prevalence of cigarette smoking, a decline in population blood pressure levels and changes in cholesterol levels were important contributors. Population-wide changes in modifiable risk factors can bring about substantial benefits and further changes in blood lipids, particularly non-high density lipoprotein (HDL) cholesterol, could be achieved through population-wide dietary changes [8]. However, limited changes in physical activity and rising levels of obesity have limited the decline in CVD mortality [8]. Further efforts are therefore needed to bring about positive changes, particularly in diet, obesity and physical activity.

### The evidence for dietary interventions

Systematic reviews of randomised controlled trials (RCTs) of generic dietary advice interventions for reducing CVD risk in the primary prevention setting have generally found small beneficial effects on mean total and low-density lipoprotein (LDL) cholesterol levels, as well as small reductions in blood pressure, but HDL cholesterol and triglyceride levels remain unchanged [9]. Most studies were conducted in the United States, with a short average duration of 10 months. Compared with usual care, dietary instruction interventions produce modest weight losses and these diminish over time [10].

### The evidence for increasing physical activity

Physical inactivity increases overall mortality and the risk of many diseases, including CVD and diabetes [11]. The Department of Health advises adults to perform at least 30 minutes of at least moderate intensity physical activity on five or more days per week, in at least 10 minute bouts, for optimum health benefits [11]. Walking is the most common form of physical activity in adults and is promoted as a near perfect exercise as it has the lowest risk of harm, and is now public health policy in the United Kingdom [12,13].

However, the proportion of those achieving these recommendations is low, particularly when objective measures are used to assess physical activity. In England, 39% of men and 29% of women self-report achieving the recommended physical activity levels, but objective assessment of physical activity using accelerometers in a sub-sample of the Health Survey for England found that only 5% of men and 4% of women aged 35 to 64 years achieved the recommended levels [14]. A Cochrane review of 17 RCTs reported moderate positive short-term increases in physical activity following health interventions, either in a group or individual format, but findings were limited since most studies used self-report measures in motivated volunteers [15]. There is mounting evidence that the use of pedometers as a method of aiding self-monitoring can increase physical activity and improve health in the short term [16]. Social support and cognitive behaviour therapy (CBT) strategies, rather than health education alone, are now recommended in older adults [17].

### The evidence for motivational interviewing

The Cochrane Heart Group systematic review of multiple risk factor interventions observed that techniques based on instruction and information such as workshops, lectures, provision of written material, assignments, shopping tours and cooking sessions were associated with small improvements in lipid levels and reductions in blood pressure, especially when embedded in a theoretical framework related to behaviour change [18]. Motivational interviewing (MI) is a common approach to behavior change in health care defined as a collaborative, goal-oriented style of communication with particular emphasis on the language of change [19]. It is designed to strengthen personal motivation for, and commitment to, a specific goal by eliciting and exploring the person’s own reasons for change within an atmosphere of acceptance and compassion [20]. An MI intervention moves through the following processes: engaging, focusing, evoking and planning. The core skills of MI can by summarised by the acronym OARS: Open question, Affirmations, Reflections and Summaries. The appeal of MI is that it is brief, can be delivered by a range of health providers and has a competency framework. Systematic reviews and meta-analyses have consistently shown that MI techniques have a moderate effect on diet and exercise (effect sizes (d) of 0.53 standard deviations in four RCTs) [21]. In another meta-analysis of MI interventions, significant effects were seen for weight reduction and for reducing cholesterol, although the number of trials was few [22].

The effects of MI can be short-lived. We found that four sessions of MI alone was not associated with improved glycaemic control in people with type 1 diabetes, but four sessions of MI followed by eight sessions of CBT was associated with improved glycaemic control (compared to usual care [23]). These effects disappeared after 12 months [24]. During the process evaluation, it was found that MI helped people to become more ready to change their behaviours, but the change was less likely to be implemented without additional support [25]. However, the evidence for enhancing MI with CBT is not consistent as the landmark Combined Pharmacotherapies and Behavioral Interventions for Alcohol Dependence study (COMBINE) did not demonstrate increased abstinence in those receiving the psychological intervention [26].

### A taxonomy of behaviour change techniques

The epidemic of modifiable risk factors for CVD and the limitations of current models of lifestyle interventions, particularly their short-term effects, is leading to a search for more sophisticated and targeted behavioural interventions [27]. For instance, systematic reviews have shown that the components of behavioural interventions that appeared to be most effective in improving diet and physical activity were based on self-regulatory behaviours such as goal setting, self-monitoring, giving feedback, utilising social support and MI. Interventions based on a psychological theory (such as the theory of planned behaviour [28]) were more effective, as were those for high risk populations. There is less evidence to support a case for any minimum threshold of intensity, mode of delivery, intervention provider and setting [18,27,29]. Strategies to prevent relapses and to increase the maintenance of healthier lifestyles over longer periods remain poorly understood and understudied. Evaluating interventions in the context of a taxonomy of behaviour change techniques and an intervention map offer a framework that is easier to teach, test, replicate and translate [28-30].

### Cardiovascular risk

The NHS Health Check programme is part of the Department of Health’s long-term vision for the future of public health in England [31]. In offering checks to all those aged between 40 and 74 years without a known diagnosis of CVD the programme aims to prevent heart disease, stroke, diabetes and kidney disease and to reduce health inequalities. The risk assessment includes collection of demographic data, family history, smoking status, cholesterol, blood pressure and a diabetes filter using computerised risk engines such as QRISK, QRISK2 or the Framingham. An individualised management plan is then given according to the risk assessment to support lifestyle changes such as referral to smoking cessation services, exercise prescriptions, lifestyle advice and signposting to local resources. However, the programme has attracted criticism due to the lack of an up-to-date evidence base for the implementation of Health Checks, and Clinical Commissioning Groups (CCGs) lacking the resources to implement them [32]. Therefore, a wider evidence base is required to substantiate the benefits of a Health Check programme. In this trial, we aim to evaluate whether MI integrated with CBT can effectively prevent development of disease in those at high risk of CVD.

### The role of health trainers and healthy lifestyle facilitators

We propose to structure our intervention, which is based on MI integrated with CBT, around health trainers. The deployment of health trainers, or healthy lifestyle facilitators (HLFs), into the public health workforce has the potential to address health inequalities; an important issue within the multi-ethnic and variably deprived South London boroughs. They are usually drawn from the local community they serve and are trained in a variety of settings with national accreditation. Their role includes identifying clients from hard-to-reach disadvantaged groups, working one-to-one to assess lifestyle and wellbeing, identifying problem areas, setting goals, supporting behaviour change and reviewing their clients’ progress [33]. The potential for a HLF to deliver more sophisticated interventions, either in an individual or a group format, has yet to be studied [34].

### Summary

The potential benefits at the population level of modifying diets, reducing weight, reducing cholesterol levels and increasing physical activity are considerable. However, identifying the most effective intervention targeting lifestyle changes remains a challenge for researchers and policy makers. MI is an intervention that has broad appeal for its collaborative patient-centred style, brevity, evidence base and deliverability. The effects of MI could be enhanced by embedding it into a taxonomy of specific health behaviour change techniques, such as setting personal goals, offering physical tools to self-monitor (such as pedometers) and offering guidance and feedback. The relative effectiveness of a group versus an individual intervention remains uncertain, but the former offers ‘automatic’ social support and may be more cost-effective.

We propose to compare the effectiveness of 10 pre-specified behaviour change techniques (integrating MI with CBT and underpinned by the theory of planned behaviour and social cognitive theory) in reducing weight and increasing physical activity in those at high risk of CVD over 24 months in two formats, group or individual, with usual care.

## Methods/Design

### Design

This is a three-arm, parallel, multicentre RCT for people identified as at high risk for CVD. The three arms are usual care, usual care and enhanced MI in a group format and usual care and enhanced MI in an individual format. As participants of the group arm, but not the other two arms, are clustered within groups we have a partially clustered (or nested) design. Simple randomisation will be used, with GP practice included as a random factor in the model, and emphasis being on more practices and fewer patients per practice. The trial is funded by the National Institute for Health Research - Health Technology Assessment Programme (NIHR-HTA) and has been registered with the International Standard Randomised Controlled Trial Number (ISRCTN) registry (identifier: ISRCTN84864870). The study flow chart in Figure 1 shows progression through the study for individual participants.

**Figure 1 Fig1:**
[figure not shown]
**Study flow chart showing progression through trial.** A 20% dropout rate is assumed.

### Primary objectives

#### Primary hypotheses

Enhanced MI, delivered in a group or individual format, is more effective than usual care in reducing weight and increasing physical activity (average number of steps per day assessed via accelerometry) 24 months later.

#### Secondary hypotheses

Enhanced MI delivered in a group format is more effective than in an individual format in reducing weight and increasing physical activity (average number of steps per day assessed via accelerometry) 24 months later.Enhanced MI, delivered in a group or individual format, is more effective than usual care in reducing LDL cholesterol, reducing CVD risk score and increasing moderate to vigorous physical activity ((MVPA) amount of at least moderate physical activity in longer than 10 minute bouts) 24 months later.Enhanced MI, delivered in a group or individual format, is more cost-effective than usual care, in terms of quality-adjusted life years (QALYs) gained over the 24 month follow-up period.

### Secondary objectives: process evaluation

#### Mediational analysis

We will conduct a mediational analysis to examine whether changes in behavioural and psychological factors such as dietary intake, health beliefs, depressive symptoms and self-efficacy mediate the association between the intervention and outcomes.

#### Effect modification and subgroup analyses

Subgroup analyses will be used to examine whether the association between the intervention and the outcomes are modified by sociodemographic, lifestyle and psychological factors measured at baseline, such as age, gender, ethnicity, family history of CVD, smoking status, alcohol intake, index of deprivation and depressive symptoms. The power for identifying significant effect modification will be limited.

#### Fidelity

A fidelity analysis (using mixed methods) will be conducted to assess whether the enhanced MI intervention is delivered according to the manual and to compare whether the level of competencies between the HLFs is associated with variations in outcomes using rating scales and thematic contents analysis of sessions.

#### Patient and therapist experience analysis

Using qualitative methods, we will describe the perceived expectations, benefits, strengths and limitations of the intervention from the patient and therapist perspective.

### Setting

The study is set in 11 South London CCGs (Bexley, Bromley, Croydon, Greenwich, Kingston, Lambeth, Lewisham, Richmond and Twickenham, Southwark, Sutton and Merton and Wandsworth) that are linked to each other by the South London Health Innovation and Education Cluster (SLHIEC), and inherent in this infrastructure is an efficient method for recruitment. South London has additional advantages: the population is nearly three million residents; nearly a quarter of the population is either African, Caribbean or South Asian; it spans the range of population densities, urbanisation and socioeconomic profiling; the development of a Health Innovation Network (HIN) in South London will allow rapid dissemination of research findings and it will be cheaper than a multicentre study across the United Kingdom, as research resources can be shared across adjacent CCGs during periods of varying workload. GP practices with list sizes greater than 5,000 patients will be invited to take part, representing approximately 60% of all practices within the SLHIEC. To recruit patients from every practice in the SLHIEC is not cost-beneficial, as smaller practices will have fewer patients to recruit from. A limitation is that the South London sample may not be representative of the rest of the United Kingdom, and not address the north and south regional health inequalities. However, there are many pockets of health inequalities within South London that mirror the rest of the United Kingdom, and we are well-placed in being in a geographical setting that has a significant proportion of Africans, Caribbeans and South Asians to address ethnicity in the design.

### Target population

The sampling frame will be GP practices with list sizes greater than 5,000 patients. The case definition includes adults aged between 40 and 74 years who screen as positive for high CVD risk, and not known to have CVD or to be on the diabetes, kidney, atrial fibrillation or stroke register. Following screening via the patient records database, the GP will invite those who are potentially eligible to participate in the study.

Informed consent is gained from all participants prior to undergoing screening in order to validate their eligibility to participate. High CVD risk will be calculated using QRISK2 (QResearch, Nottingham, UK), a validated predictive tool for identifying those at a 20% or higher chance of having a fatal or non-fatal cardiovascular event over the next 10 years [35]. The measures required for the calculation of QRISK2 score are age (years), smoking status, self-assigned ethnicity, systolic blood pressure, ratio of total serum cholesterol to HDL cholesterol, body mass index (BMI), family history of coronary heart disease in first degree relative, Townsend deprivation score, treated hypertension and diagnosis of rheumatoid arthritis.

### Criteria for including and excluding patients

The inclusion criteria are: fluent in conversational English, permanent residents and planning to stay in the United Kingdom for at least three quarters of the year and at high cardiovascular risk according to GP records (QRISK2 score ≥20%).

The exclusion criteria are: established CVD (including congenital heart disease, angina, myocardial infarction, coronary revascularisation procedures, peripheral artery disease, coronary artery bypass graft or angioplasty); having a pacemaker; on a register for diabetes, kidney disease, atrial fibrillation or stroke (either ischemic or haemorrhagic, including transient ischemic attacks); chronic obstructive pulmonary disease; disabling neurological disorder; severe mental illness such as psychosis, learning disability, dementia and cognitive impairment; registered blind; housebound or resident in nursing home; unable to move about independently or not ambulatory; more than three falls in past year; pregnancy; advanced cancer; morbid obesity (BMI ≥50 kg/m^2^); and current participation in a weight loss programme. When in doubt we will seek the GP opinion and approval.

### Sample size

The power calculation of our main outcome variables are based on the findings of previous research [16,36]. We have selected a very conservative effect size of 0.25 expressed as the difference in units of pooled standard deviations, which translates to an ability to detect a difference between two groups of 675 steps per day (physical activity), 1.25 kg weight and 0.25 umol/l total cholesterol at 24 month follow-up. Our study is powered to detect changes which may be modest at the individual level, but would have an important impact if occurring at the population level [37].

We took into account clustering effect within the group intervention (intraclass correlation coefficient = 0.05) by calculating the optimal sample size in presence of differential clustering effects [38]. A sample size of 1,420 participants in total are needed to detect these differences in our primary hypotheses, and a two-tailed alpha of 0.025 to take account of multiple comparisons of the contrasts ‘individual intervention versus control group’, ‘group intervention versus control group’ and ‘group versus individual intervention’. Assuming an approximate dropout rate of 20%, a total sample size of 1,704 (540 in group and 440 in individual and usual care) is needed.

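### The 20% dropout allowance is computed as 1,420 × 1.2 = 1,704 rather than 1,420 / 0.8 = 1,775, and the arm sizes printed beside 1,704 add up to 1,420

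*Protocol article*

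**What the plan says.** The Sample size section gives the requirement as "A sample size of 1,420 participants in total are needed to detect these differences in our primary hypotheses". It then allows for attrition: "Assuming an approximate dropout rate of 20%, a total sample size of 1,704" participants, with the arm sizes in parentheses, "540 in group and 440 in individual and usual care) is needed". The legend of Figure 1 repeats the rate without qualification: "A 20% dropout rate is assumed". The abstract carries the total forward: "A sample of 1,704 participants will be randomised". The Trial status section also gives 1,704 as the number to be randomised.

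The other design inputs are in the same Sample size section: "We have selected a very conservative effect size of 0.25 expressed as the difference in units of pooled standard deviations"; "a two-tailed alpha of 0.025 to take account of multiple comparisons of the contrasts"; and "We took into account clustering effect within the group intervention (intraclass correlation coefficient = 0.05". The section on randomisation and allocation concealment sets a 4:3:3 ratio for group, individual and usual care. The intervention description gives a typical therapy group as 10 to 11 people. The article prints neither the inflation formula nor a target power.

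**The concern.** Read together, the two Sample size sentences say that 1,420 participants with outcome data are required and that randomising 1,704 secures them if one in five is lost. It does not. The 20% was added to the number required, when it should have been taken off the number randomised. The sentence therefore attaches to 1,704 a property that the figure lacks.

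The parenthesis adds a second fault: the three arm sizes offered as the breakdown of 1,704 total 1,420. From this text a reader cannot tell how many participants each arm is meant to randomise and how many it is expected to retain.

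The practical stake is how attrition will be judged. Dropout of 18%, for example, would look within plan, yet 1,704 × 0.82 ≈ 1,397, below the stated requirement.

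**Working it through.** **1. Reproduce the plan's figure.** Inputs from Sample size: required n = 1,420, dropout d = 0.20.
- n × (1 + d) = 1,420 × 1.2 = 1,704, exactly the printed total.
- n / (1 − d) = 1,420 / 0.8 = 1,775, which is 71 more.

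**2. What 1,704 delivers.**
- Retained at 20% dropout: 1,704 × 0.8 = 1,363.2, about 1,363.
- Shortfall: 1,420 − 1,363.2 = 56.8, about 57; 56.8 / 1,420 = 4.0%.
- Dropout at which 1,420 remain: 1 − 1,420 / 1,704 = 16.7%.

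**3. Is 1,420 the number before the dropout allowance?**
- 540 + 440 + 440 = 1,420.
- The total can be rebuilt from the plan's inputs without any dropout term. Take effect size 0.25, two-sided alpha 0.025 (z = 2.241), ICC 0.05, 11 per therapy group, and an assumed power of 90% (z = 1.282). The design effect is DE = 1 + (11 − 1) × 0.05 = 1.5, with √DE = 1.225.
- With optimal allocation, usual care (and individual) needs ((2.241 + 1.282) / 0.25)² × (1 + 1.225) ≈ 442, and group needs 442 × 1.225 ≈ 541. The total is about 1,425, close to 1,420. With 10 per group it is about 1,402.
- So 1,420 already contains clustering and the adjusted alpha, and no allowance for loss.

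**4. Arm sizes that fit 1,704.** At 4:3:3: 1,704 × 0.4 = 681.6 and 1,704 × 0.3 = 511.2, about 682/511/511. The printed 540:440 is 1.23:1, whereas 4:3 is 1.33:1.

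**5. Power cost, like for like.** Both totals are split 4:3:3, with 10.5 per therapy group (midpoint of 10 to 11), so DE = 1 + 9.5 × 0.05 = 1.475. Normal approximation: power = Φ(0.25 / SE − 2.241). For group versus usual care, SE = √(1.475 / n_group + 1 / n_usual care). For individual versus usual care, SE = √(2 / n per arm).

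| 24-month completers | Arms (group/individual/usual care) | Group v usual care | Individual v usual care |
|---|---|---|---|
| 1,420 | 568/426/426 | SE 0.0703, power 90.6% | SE 0.0685, power 92.0% |
| 1,363 | 545/409/409 | SE 0.0718, power 89.3% | SE 0.0699, power 90.9% |

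Each contrast loses a little over one percentage point. With 10 or 11 per group, the group-contrast figures move by about 0.3 points.

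**The case against.** The plan calls the rate approximate, and multiplying by one plus the dropout rate is a common shortcut. Neither point rescues the figure. The total was built with exactly 0.20, the Figure 1 legend gives 20% flatly, and at that rate 1,704 falls short of the plan's own requirement.

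The stronger objections concern how much follows from the error, and they stand.

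- **An underpowered trial.** A reader might infer this, but the numbers do not support it. If 20% loss also shrinks the therapy groups to about 8.4 members with outcomes (10.5 × 0.8; DE = 1 + 7.4 × 0.05 = 1.37), group versus usual care has about 90.5% power with 1,363 completers, against 91.7% with 1,420. The loss is again about one point, and both contrasts stay near 90%.
- **A two-point loss for individual versus usual care.** Setting the printed 540/440/440 (92.9% for that contrast) against 545/409/409 (90.9%) suggests this. That comparison mixes dropout with a change of allocation ratio; at a constant 4:3:3 the fall is from 92.0% to 90.9%.
- **Only 1,363 participants can be analysed.** The figure counts 24-month completers. The planned mixed model uses both the 12- and 24-month assessments and relies on missing at random, so participants seen only at 12 months still contribute. This may soften the loss, although the sample size section takes no credit for it.
- **A wrong consent target.** Trial status reports 40 to 50% of those consented as ineligible, so 3,000 consented yields 1,500 to 1,800. Both 1,704 and 1,775 lie in that range, so the error is not shown to alter the 3,000.

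**Conclusion.** The point holds as a minor arithmetic error in the central sample size statement. At 20% dropout, 1,704 randomised gives about 1,363 completers at 24 months, 57 (4.0%) below the stated 1,420. It protects 1,420 only up to 16.7% dropout; at 20% the total would have to be 1,775. The arm sizes given for 1,704 are those of 1,420. These conclusions use only printed figures.

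The power cost, about one percentage point per contrast with usual care, rests on a normal approximation, 4:3:3 allocation among completers, equal dropout across arms and 10.5 members per therapy group. The 90% power used to rebuild 1,420 is an assumption, and the arithmetic error does not depend on it. The hypotheses, contrasts and analysis model are unaffected.

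**What to change.** Correct the sentence in one of these ways:

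- state that 1,704 randomised gives about 1,363 24-month completers at 20% dropout; or
- state that 1,704 allows for 16.7% dropout from a requirement of 1,420; or
- only if 1,420 completers at 20% dropout is to remain the claim, change the total to 1,775.

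In the same edit, label 540/440/440 as the numbers needed before the dropout allowance, and give the randomised arm sizes that match the total (about 682/511/511 for 1,704 at 4:3:3). Bring the Figure 1 legend into line if the dropout rate is changed, and the abstract and Trial status if the total is.

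Either of the first two options costs wording only and no extra participants. The third means randomising 71 more.

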### Randomisation and allocation concealment

Randomisation of participants will be conducted by the data manager from an independent Clinical Trials Unit (King's College London) using computer-generated randomisation blocks with block sizes of 10. In each block, 10 subjects will be randomised to group, individual or usual care in a 4:3:3 ratio. The unequal allocation ratio ensures that the group arm will have approximately 33% more patients, allowing the group sessions to run with a sufficient number of participants. As this is a complex intervention, it is not possible to conceal the allocation to the participants or the HLFs. Assessors and technicians will be blind to the allocation for the primary and secondary outcomes. There is a small inevitable risk that allocation will be revealed to the outcome assessors, which will be minimised by requesting and reminding participants not to reveal their allocation.

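### The arm sizes printed for 1,704 add up to the pre-dropout 1,420 and do not follow 4:3:3, and the randomisation method is given as both simple and blocked

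*Protocol article*

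**What the plan says.** All of this is in the Methods/Design part of the protocol article.

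- **Sample size.** The requirement is first put at 1,420. With about 20% dropout, the text then puts the total needed at "1,704 (540 in group and 440 in individual and usual care".
- **Randomisation and allocation concealment.** The sequence uses "computer-generated randomisation blocks with block sizes of 10", and "10 subjects will be randomised to group, individual or usual care in a 4:3:3 ratio". The section adds that "The unequal allocation ratio ensures that the group arm will have approximately 33% more patients", and gives the reason: the group sessions need enough participants to run.
- **Design.** "Simple randomisation will be used, with GP practice included as a random factor in the model". No ratio is given here.
- **Abstract and Trial status.** Both treat 1,704 as the number to be randomised.

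**The concern.** There are three separate faults: a sum, a ratio and a method. The bracketed arm sizes do not add up to the total they are meant to break down. Their proportions differ from the ratio in the randomisation section. The Design section also names a procedure that is not the one described later. Simple randomisation lets arm counts drift by chance, whereas fixed blocks hold them to the ratio.

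As printed, a reader cannot take arm targets for 1,704 from the Sample size section, cannot tell what power the allocation in use provides, and could report the wrong method of sequence generation. The article commits itself to CONSORT reporting, where arm sizes and sequence generation are compared with what was done.

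**Working it through.** **Inputs.** From Sample size: 1,420 before dropout; 1,704 after; dropout 20%; arms 540/440/440; effect size d = 0.25 SD; two-sided alpha 0.025; intraclass correlation 0.05 in the group arm. From Randomisation and allocation concealment: 4:3:3. From Intervention development: therapy groups of 10 to 11. The article states no power; where a target is needed below, 90% is assumed.

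**1. Reproduce the total.** 1,420 × 1.20 = 1,704, so the plan's figure is reproduced. Dividing instead, 1,420 / 0.80 = 1,775. With 20% lost from 1,704, 1,704 × 0.80 = 1,363 remain, which is 57 fewer than 1,420.

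**2. Sum the arms.** 540 + 440 + 440 = 1,420. This is 284 short of 1,704 and exactly the pre-dropout total. Reading 440 as individual and usual care combined gives 980, which fits neither total.

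**3. Compare the ratios.** 540/440 = 1.227, an excess of 23%. 4/3 = 1.333, an excess of 33%.

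| Total | At 4:3:3 | At 540:440:440 |
|---|---|---|
| 1,420 | 568/426/426 | 540/440/440 |
| 1,704 | about 682/511/511 | 648/528/528 |

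No 4:3:3 split of either total gives 540/440/440.

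**4. Where 540/440/440 probably comes from.** With clustering in one arm only, the design effect is DE = 1 + (m − 1) × 0.05, which is 1.45 for m = 10 and 1.50 for m = 11. The optimal ratio of group to control is √DE, or 1.204 to 1.225. The control arm size is n = (z₀.₉₈₇₅ + z₀.₉₀)² / 0.25² × (1 + DE/√DE). At m = 11 and 90% power this is (2.241 + 1.282)² / 0.0625 × 2.225 ≈ 442, with 541 in the group arm and 1,425 in all. At m = 10 the total is 1,403. At 80% power it would be only about 1,074 to 1,091. So 540/440/440 looks like evaluable numbers from an optimal-allocation calculation at about 90% power.

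**5. Power for each set of evaluable numbers.** Power = Φ( d / √(DE/n_group + 1/n_usual) − 2.241 ), with DE = 1 for individual v usual care. This is a normal approximation without baseline adjustment. The ranges cover m = 10 to 11.

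| Evaluable | Group v usual care | Individual v usual care |
|---|---|---|
| 540/440/440 | 89.9% to 90.5% | 92.9% |
| 568/426/426 (4:3:3 of 1,420) | 90.3% to 90.8% | 92.0% |
| 545/409/409 (4:3:3 of 1,704, 20% lost) | 89.0% to 89.6% | 90.9% |

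Worked example, last row, individual v usual care: 0.25 / √(2/409) = 3.575; 3.575 − 2.241 = 1.334; Φ(1.334) = 0.909.

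The change of ratio alone moves power by less than one point. The rest comes from the shortfall of 57.

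**6. Method.** No arithmetic applies. Independent draws and fixed blocks of 10 are different procedures, and the article names both.

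**The case against.** The best defence is that the randomisation section is coherent and operational: blocks of 10 at 4:3:3 do give a group arm one third larger. Its stated reason is practical, to fill the group sessions, and it does not claim to be the statistical optimum. Choosing a workable ratio close to the optimum is legitimate. In the Design section, the word simple may loosely mean not stratified by practice, since the sentence goes on to handle practice in the model. All of this is fair, and it makes blocks the likelier procedure. It does not make the two descriptions agree, nor does it correct the bracketed arm sizes. The study flow chart, which might show arm sizes at randomisation, is not reproduced in the text available. Even if it is right, the sentence in Sample size stays wrong.

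Two stronger readings are tempting, and the article does not support them.

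- **Three incompatible allocations.** A reader might count simple randomisation, 4:3:3 and 540/440/440 as three rival allocations. Simple randomisation names no ratio, so it cannot conflict with 540/440/440. The conflicts are one of method and one of ratio, plus the sum error.
- **Under-recruitment in every arm.** A reader might take 540/440/440 as the numbers to randomise. After 20% loss, 432/352/352 would remain, with power of about 82% and 86%. But the Abstract says 1,704 will be randomised, and Trial status raises recruitment to 3,000 in order to reach that number. Stopping at 1,420 would contradict both.

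**Conclusion.** The point stands as an error in the text with a small statistical effect. The arm sizes attached to 1,704 belong to 1,420, their ratio is not the one used to randomise, and the method is described in two ways.

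For the allocation that 1,704 at 4:3:3 would deliver, power falls by about 1 to 2 points from that of 540/440/440 evaluable, to about 89% (group v usual care) and 91% (individual v usual care). The individual and usual care arms would each end about 31 below the 440 given in the Sample size section, while the group arm would end about 5 above 540.

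These power figures rest on the article's effect size, alpha, intraclass correlation and group size, on dropout of 20% in every arm, and on an unadjusted comparison. The planned model adjusts for baseline, which would normally raise power in all rows. The 90% target behind the reconstruction is an assumption.

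**What to change.** 1. **Design section.** Make it agree with the randomisation section: unstratified block randomisation, blocks of 10 at 4:3:3, once the trials unit confirms that this is what it runs.
2. **Sample size section.** Label 540/440/440 as the evaluable numbers behind 1,420. Then give the arm sizes that 4:3:3 of 1,704 delivers: about 682/511/511 randomised and 545/409/409 (1,363) evaluable at 20% dropout.
3. **Shortfall.** Say openly that 1,363 is below 1,420 because the allowance was made by multiplying by 1.20. Dividing by 0.80 would give 1,775. Without this sentence, the corrected paragraph would show a new discrepancy unexplained.
4. **Power.** State it for the delivered sizes, about 89% and 91%, with the assumptions beside it.

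The cost is a few sentences and one query to the trials unit. Nothing changes in conduct if blocks of 10 at 4:3:3 are already in use. Whether to raise the total towards 1,775 is a separate decision that this correction does not force.
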